**5.3 Withdrawal of individual subjects**

Participants can leave the study at any time for any reason if they wish to do so without any consequences. The investigator can decide to withdraw a participant from the study for urgent medical reasons. In case of withdrawal all stored data and results of previously analysis will not be destroyed except when the participant asks for destruction of the data. Consequently, the results of the data will also be destroyed.

**6. SAFETY****6.1 Section 10 WMO event**

In accordance to section 10, subsection 1, of the WMO, the investigator will inform the subjects and the reviewing accredited METC if anything occurs, on the basis of which it appears that the disadvantages of participation may be significantly greater than was foreseen in the research proposal. The study will be suspended pending further review by

**Protocol ID NL42367.018.12****Reflux symptoms in achalasia**

the accredited METC, except insofar as suspension would jeopardise the subjects' health. The investigator will take care that all subjects are kept informed.

**6.2 Adverse events and serious adverse events**

All the measurements that are performed are safe procedures and routinely performed in the clinical setting, with rarely any serious complications. Possible complications are mainly due to placement of the catheters. The catheters can give discomfort in the nose and pharynx. Furthermore in rare cases a mucosal bleeding of the nose, caused by the catheter, can occur which never need extra treatment. All adverse events reported spontaneously by the subject or observed by the investigators will be recorded in a database.

All serious adverse events (SAEs) will be reported through the web portal *ToetsingOnline* to the accredited METC that approved the protocol. The SAEs will be reported within 15 days after the sponsor is first notified of the SAEs.

The SAEs that result in death or are life treating will be reported expedited through the web portal *ToetsingOnline* to the accredited METC that approved the protocol. This will not occur later than 7 days after the coordinating investigators and principal investigator have knowledge of the SAE(s). This first report is preliminary and within 8 days after submission of the first report a final report will be submitted.

**6.3 Follow-up of adverse events**

All adverse events will be followed until they have abated or until a stable situation has been reached. Depending on the event, follow up may require additional tests or medical procedures as indicated, and/or referral to another medical specialist.

**6.4 Annual safety report**

Not applicable for this study.

**7. PRIVACY**

The data of the subjects are coded in order of participation. This code will identify participants throughout documentation and evaluation. The code does not obtain elements of the name or date of birth of the participants. The code and the data are stored in different locations. The code can only be seen by the investigators. The participants will be told that all study findings will be stored on the computer and handled in strict confidence according to national guidelines. Study data will be stored 20 years after closure of the study.

## 8. STATISTICAL ANALYSIS

Statistical analysis will be performed in collaboration with the department of Biostatistics and Epidemiology of the University of Amsterdam. After testing for normality, unpaired testing will be performed between the two treatment groups for all primary and secondary outcome parameters. Categorical variables will be compared using the Chi-square test. Comparison of the numerical variables will be dependent of the distribution of the data.

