## 2. OBJECTIVES

Our hypothesis is that gastroesophageal reflux symptoms in treated patients with achalasia are dependent on retention and fermentation of food due to a reduced clearance by aperistalsis of the esophageal body rather than the result of true acid reflux episodes. We expect a difference in gastroesophageal reflux episodes, LES pressure, sensitivity to acid and esophageal distension in the treated patients with achalasia that experience

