### 4.4 Sample size

Treated achalasia patients with or without gastroesophageal reflux symptoms will be included. Per group we aim to include 20 study subjects. In the literature the incidence of GER symptoms in patients with achalasia post-treatment is very variable. Articles describe an incidence that differs between 10% up till 60%. This variability in the incidence is probably caused by the different diagnostic approaches in these studies. Furthermore the GER symptoms do not always correlate with a positive pH-impedance monitoring for GERD or fermentation of food.

Based on this we expect that 30% of the patients without GER symptoms will have gastroesophageal reflux episodes caused by GER or fermentation of food. For the patients with GER symptoms we estimate that in 75% gastroesophageal reflux episodes occur caused by GER or fermentation. We consider a 45% difference in gastroesophageal reflux episodes between the two groups as clinically relevant. When, using a two-group chi-square test with a two-sided significance level of 5% and a power of 80%, the sample size required in each group is 19 subjects. Based on this we aim to include 40 study subjects. Below we have calculated the sample sizes based on our main secondary study parameters to show that with a sample size of 40 study subjects it is possible to attain these secondary study parameters.

We believe that the three main secondary study parameters are LES pressure, esophagogastric junction distensibility and the level of esophageal stasis. Several studies have described that true GERD occurs in patients with a lower mean LES pressure post-treatment. However, other studies contradict these findings. Based on our hypothesis we believe that patients with GER symptoms have a higher mean LES pressure post-treatment

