**5. METHODS****5.1 Study parameters****5.1.1 Primary study parameter**

- Gastroesophageal reflux episodes

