**Protocol ID NL42367.018.12****Reflux symptoms in achalasia**

pH 7 and pH 1. The catheter will be positioned in such a way that the pH sensor is located 5 cm above the LES, which is based on manometry readings.

*Analysis of the data of the HRM and pH-impedance monitoring*

For analysis of the data obtained with HRM and pH-impedance measurement MMS software (Enschede, The Netherlands) will be used. Observers will be blinded for patient characteristics when analyzing the measurement.

The HRM will give insight in the esophageal function. It provides information on the contractile activity of the esophageal body and the esophagogastric junction including the LES. Therefore it is helpful in distinguishing transient LES relaxation (TLESRs), which occurs in GERD, from pseudorelaxation of the LES by shortening of the esophageal body. pH-impedance monitoring provides information on esophageal bolus transit. Combined with HRM it can distinguish GER from retention and fermentation of food. GER is characterized by TLESRs and a retrograde moving decrease in impedance with an abrupt drop in pH levels followed by normalisation of the impedance and pH. In case of fermentation there is a slow and longer decrease in impedance and pH. The pH-impedance monitoring will also record all reflux episodes, both acid as non-acid, during the 24-hours measurement. During the analysis of the data of the pH-impedance monitoring reflux symptoms will be correlated with acid and non-acid reflux episodes. A positive correlation is declared if a specific reflux symptom is preceded by a reflux episode within two minutes.

*Acid perfusion test*

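### The plan pools true reflux with fermentation and names no comparison between them, so it cannot support its hypothesis that symptoms come from one rather than the other

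*Protocol*

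**What the plan says.** **Hypothesis.** Section 2 attributes symptoms to retention and fermentation of food "rather than the result of true acid reflux episodes". It then gives expected differences between patients with and without symptoms: "We expect a difference in gastroesophageal reflux episodes, LES pressure, sensitivity to acid and esophageal distension in the treated patients".

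**Primary parameter.** Section 5.1.1 lists "Gastroesophageal reflux episodes", not divided by mechanism. Section 4.4 plans on the two causes together: it expects that "30% of the patients without GER symptoms will have gastroesophageal reflux episodes caused by GER or fermentation of food", and for patients with symptoms that "in 75% gastroesophageal reflux episodes occur caused by GER or fermentation".

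**Measurement.** Section 5.2.2, on analysis of the HRM and pH-impedance data, says of pH-impedance: "Combined with HRM it can distinguish GER from retention and fermentation of food". It describes a different impedance and pH pattern for each. It also plans to relate symptoms to acid and non-acid reflux episodes with a two-minute rule. Fermentation episodes are not part of that rule.

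**Tests.** Section 8 states that "unpaired testing will be performed between the two treatment groups for all primary and secondary outcome parameters" and that "Categorical variables will be compared using the Chi-square test". (The groups are defined by symptoms, not by treatment.)

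**The concern.** The hypothesis ranks two mechanisms. To support it, an analysis must show that fermentation is more strongly tied to symptoms than true reflux is. The primary comparison adds the two together, so it cannot do this. The measurements that could separate them are taken, but no named analysis uses the separation.

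Without a stated contrast, the likely substitute is to test each pattern between the groups and compare the two p-values. One significant and one non-significant result does not show that the two effects differ. The introduction says that the answer could influence the choice of initial treatment, so a mechanism claim made this way could have practical consequences.

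**Working it through.** **1. The plan's own figure.** Inputs from section 4.4: 30% and 75%, two-sided 5%, 80% power, chi-square test. With pooled variance, mean proportion 0.525 and no continuity correction:

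n = [1.960 × √(2 × 0.525 × 0.475) + 0.842 × √(0.30 × 0.70 + 0.75 × 0.25)]² / 0.45² = 18.1, so 19 per group.

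The stated 19 is reproduced. By the same approximation, power is 82% at 19 and 84% at 20 per group.

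**2. What that comparison can show.** Suppose the 75% is all fermentation, all true reflux, or half of each. The contrast is 0.75 − 0.30 = 0.45 in every case, so a significant result says nothing about which mechanism is at work.

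**3. Two separate between-group tests.** The protocol gives no split, so these are assumptions chosen to keep its totals. There are 20 patients per group, tested by uncorrected chi-square at two-sided 5%.

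- *Independent mechanisms, equally common.* Symptomatic: 50% each, since 1 − 0.50² = 0.75. Symptom-free: 16.3% each, since 1 − 0.837² = 0.30. Each test has power 0.651. Fermentation significant and reflux not: 0.651 × (1 − 0.651) = 22.7%.
- *Mutually exclusive mechanisms, equally common.* Symptomatic: 37.5% each (total 75%). Symptom-free: 15% each (total 30%). By simulation of 400,000 trials: about 29%.

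In 23% to 29% of trials, then, the result would appear to favour fermentation although neither mechanism prevails.

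**4. A contrast that answers the question.** Score each pattern 0 or 1 in each patient and take D = fermentation − GER. The between-group difference in mean D is

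(F in symptomatic − F in symptom-free) − (G in symptomatic − G in symptom-free),

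which is how much more strongly fermentation than reflux is associated with symptoms. Each patient contributes one value of D and the groups are independent, so an unpaired test is correct.

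With independent patterns, the variance of D is F(1 − F) + G(1 − G). In symptom-free patients at 16.3% each, mean D is 0 and the variance is 2 × 0.163 × 0.837 = 0.273.

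| Symptomatic F, G | Mean D | Variance of D | Standard error of the difference | Ratio | Simulated power |
|---|---|---|---|---|---|
| 65%, 30% | 0.35 | 0.2275 + 0.21 = 0.4375 | √[(0.4375 + 0.273)/20] = 0.188 | 1.86 | about 45% |
| 70%, 17% | 0.53 | 0.21 + 0.141 = 0.351 | √[(0.351 + 0.273)/20] = 0.177 | 3.00 | about 82% |

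When the mechanisms are equally common, or when both groups have the same rates, this contrast wrongly favours fermentation in about 2.5% of trials, the nominal one-sided error.

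**5. Why a paired test in the symptomatic group cannot carry the claim.** An exact McNemar test in the 20 symptomatic patients asks which pattern is commoner there and ignores the symptom-free group.

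- Fermentation 70% and GER 17% in *both* groups, so neither relates to symptoms: McNemar favours fermentation in 89% of trials.
- Fermentation 80% in both groups and GER 30% against 5%, so only reflux tracks symptoms: McNemar still favours fermentation in 83%.

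**The case against.** **Section 8 excludes nothing.** A reader might infer that it permits unpaired tests only. It says that they will be performed for the listed parameters and does not rule out other analyses, and an SAP that is not shown may add some. This stands. The point is that the protocol states a ranking hypothesis, pools the two things to be ranked, and names no analysis that separates them.

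**The expectations are framed between groups.** Section 2 expects differences between the symptom groups. Section 4.4 predicts higher LES pressure, lower EGJ distensibility and more stasis in symptomatic patients. Unpaired tests suit these, and the results would bear on mechanism. This stands too, but the evidence is indirect: more stasis in symptomatic patients does not show that fermentation rather than reflux accounts for their symptoms.

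**A symptom correlation is planned.** It asks within each recording whether reflux precedes symptoms, which is half of the hypothesis. With no fermentation counterpart it cannot compare the two, but it does mean that comparing p-values is not the only evidence available.

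**The hypothesis calls for pairing.** A reader might infer that, because both patterns come from one recording, Section 8 is wrong to use unpaired tests and a McNemar or signed-rank test should decide. Step 5 shows otherwise. The hypothesis concerns what symptoms depend on, so the symptom-free group is needed. Section 4.4 itself expects some stasis in achalasia patients without complaints.

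**The 23% to 29% is not a formal error rate.** Correct. It is the frequency of a misleading result pattern, and becomes an error only if superiority is read from it. The protocol plans neither the two tests nor that reading.

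**Conclusion.** The concern holds in this form: the hypothesis sets fermentation against true reflux, the primary comparison merges them, and no named analysis contrasts them. As written, the plan can show that symptomatic patients have more episodes of either kind, with indirect evidence from pressure, distensibility and stasis. It cannot support the ranking.

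The size rests on assumed splits that keep the protocol's 75% and 30%. Two separate tests would point to fermentation alone in about 23% (independent mechanisms) to 29% (exclusive mechanisms) of trials when neither prevails. The between-group contrast of per-patient differences keeps that near 2.5%, with power of about 45% to 80% depending on how far one mechanism dominates.

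The documents do not support the stronger reading that unpaired testing is itself the fault. The contrast that answers the question is an unpaired one. What is missing is the separation of the two outcomes and a stated comparison.

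**What to change.** In section 8:

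- Analyse GER and fermentation as separate outcomes, using the patterns in section 5.2.2, on the same scale. Presence or absence of each in each patient is the simplest choice, since episode counts of abrupt and slow events may not be comparable.
- Compare the per-patient difference (fermentation minus GER) between symptomatic and symptom-free patients with an unpaired test and a 95% confidence interval. State that any claim that symptoms depend on fermentation rather than reflux will rest on this contrast.
- Label any McNemar or signed-rank comparison within the symptomatic group as a description of which pattern is commoner there.

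In section 5.2.2, apply the symptom-association rule to fermentation episodes as well as reflux episodes.

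The cost is a few sentences and a working definition of when each pattern counts as present. No extra patients, procedures or recordings are needed, and the 19-per-group calculation for the pooled endpoint is unaffected. The drawback is moderate power with 20 per group unless one mechanism clearly dominates. The report should say so and should not read a non-significant contrast as evidence that the mechanisms matter equally.

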## 9. ETHICAL CONSIDERATIONS

### 9.1 Regulation statement

The procedures set out in this study protocol are designed to ensure that the investigators abide by the principles of the good clinical practice guidelines of the European Union and the Declaration of Helsinki in the conduct, evaluation and documentation of the study. The protocol of this study will be submitted to the Medical Ethical Committee of the Academic Medical Centre and will not start before formal approval has been granted.

### 9.2 Recruitment and consent

Participants will be given oral explanation about the study and receive an information letter including an informed consent form. Patients will be given sufficient time to read the information and ask questions. Before any study procedures are initiated the patient must sign the informed consent form. Participants are allowed to withdraw informed consent without providing arguments.

Patients with achalasia with or without gastroesophageal reflux symptoms are suitable candidates for the study and will be recruited from the outpatient clinic. Patients that fulfill the criteria are asked to participate in the study.

### 9.3 Benefits and risks assessment

Benefits and risks of study participation are both nearly absent. The study can provide more insight in the mechanism behind GER symptoms in treated achalasia patients. Therefore it could be possible to improve the treatment of these patients and the results might even influence the choice of the initial treatment of achalasia.

### 9.4 Compensation for injury

**Protocol ID NL42367.018.12****Reflux symptoms in achalasia**

The investigator has a liability insurance which is in accordance with article 7, subsection 9 of the WMO.

This insurance provides cover for damage to research subjects through injury or death caused by the study.

1. € 450.000,-- (i.e. four hundred and fifty thousand Euro) for death or injury for each subject who participates in the Research;
2. € 3.500.000,-- (i.e. three million five hundred thousand Euro) for death or injury for all subjects who participate in the Research;
3. € 5.000.000,-- (i.e. five million Euro) for the total damage incurred by the organisation for all damage disclosed by scientific research for the Sponsor as 'verrichter' in the meaning of said Act in each year of insurance coverage.

The insurance applies to the damage that becomes apparent during the study or within 4 years after the end of the study.

**9.5 Incentives**

There is an incentive of 150 euro per study subject for participation in the project and compensation for travel expensons. Regular treatment by the local Gastroenterologist is not influenced by participation or refusal.

**10. ADMINISTRATIVE ASPECTS AND PUBLICATION****10.1 Handling and storage of data and documents**

All the stored data and documents will be coded with a study number, in order of participation, and the date of inclusion. The code is unique for every participant that contributes to this study and does not obtain elements of the name or date of birth of the study subjects. This code will identify study subjects throughout documentation and evaluation. The code of the data of the participants is stored in different locations. Therefore, this code will not be directly traceable to the participant. Only the involved investigators will have access to the code. The participants will be told that all study findings will be stored on the computer and handled in strict confidence according to national guidelines.

The principal investigator and the main investigator will have access to the code and the data. Auditors, monitors and the Health Care Inspectorate will have access to the data. The data will not be available to other reachers. After closure of the study, the study data will be stored for 20 years.

**Protocol ID NL42367.018.12****Reflux symptoms in achalasia**

Study subjects can only be included in the study when written informed consent is given. During the study, participants can withdraw consent at any time for any reason without any consequences. By withdrawal of the study no additional information of the participants will be collected. The stored data and results of previously analysis will not be destroyed if a study subject withdrawals. But participants keep the right to ask for destruction of the data and consequently the results, even after closure of the study. Collecting of extra data or performing more measurements is only allowed when the participant gives a new written informed consent.

**10.2 Amendments**

Amendments should be made only in exceptional cases once the study has started. Changes must be agreed to in writing, and signed, by all parties concerned. The changes then become part of the study protocol. The medical ethics committee must be informed of all amendments and if necessary approval must be sought for ethical aspects.

**10.3 Annual progress report**

The investigator will submit a summary of the progress of the study to the accredited METC once a year. Information will be provided on the date of inclusion of the first subject, numbers of subjects included and numbers of subjects that have completed the study, serious adverse events/ serious adverse reactions, other problems, and amendments.

**10.4 End of study report**

The investigator will notify the accredited METC of the end of the study within a period of 8 weeks. In case the study is ended prematurely, the investigator will notify the accredited METC, including the reasons for the premature termination. Within one year after the end of the study, the investigator will submit a final study report with the results of the study, including any publications/abstracts of the study, to the accredited METC.

